## Abstract

**Background:**

Long Covid is a term used to describe a multisystem condition that presents with a myriad of physical and psychological symptoms that continue or develop after acute COVID-19. Long Covid is a significant public health problem because of the nature of the illness, its negative impfact on everyday functioning, and the healthcare inequalities evident in access and experience, notably in terms of ethnicity and socioeconomic status. Evidence in patients hospitalised with their acute infection suggests exercise-based rehabilitation could be helpful to improve exercise tolerance, respiratory symptoms, fatigue, and cognition; however, research is needed to determine whether exercise-based rehabilitation is effective and acceptable for patients with Long Covid who were not hospitalised.

**Methods:**

This mixed-methods study comprises a single-centre, randomised controlled trial to determine whether face-to-face rehabilitation increases exercise capacity compared to usual care alone in non-hospitalised patients with Long Covid, with embedded qualitative components to explore intervention acceptability in the context of healthcare inequalities. Usual care is as defined by the National Institute for Clinical Excellence (NICE) Covid-19 guidance.

The rehabilitation intervention will take place twice a week for 6 weeks and will combine symptom-titrated exercise with self-management education. The proposed sample size of 56 for the randomised controlled trial is calculated on the primary outcome of Incremental Shuttle Walking Test (ISWT) distance, with a change of 50metres (m) at 90% power, a standard deviation of 17 m, and a 0.05 type 1 error.

**Discussion:**

A mixed-methods approach has been chosen as quantitative data alone would be insufficient to answer the research question, and mixing the data will enable a more comprehensive understanding and ensure there is an equal focus on outcomes and experiences of a face-to-face exercise-based rehabilitation programme. A healthcare inequalities lens will explore who may be under-represented, with the qualitative work providing further evidence as to why this may be the case. It is recognised that meeting recruitment targets in the context of reducing referral rates and funding for Long Covid services may prove challenging.

**Trial registration:**

ISRCTN trial registry (ISRCTN33340595). Registered on 30 September 2024.

**Supplementary Information:**

The online version contains supplementary material available at 10.1186/s13063-025-09419-z.

## Introduction

### Background and rationale {6a}

Long Covid, a term preferred by patient advocates, is defined by NICE as follows: ‘a multi-system condition with a range of debilitating symptoms — signs and symptoms continue or develop after acute COVID-19, continue for more than 4 weeks, and are not explained by an alternative diagnosis’ [1].

Patients with Long Covid present with a myriad of symptoms that can include fatigue, shortness of breath, headache, cognitive dysfunction (‘brain fog’), chest pain, muscle and joint pains, cough, disturbed sleep, and psychological symptoms, such as anxiety and depression [2, 3]. These symptoms are often unpredictable and concurrent, which can significantly negatively impact everyday functioning and occupation [4]. It is difficult to substantiate the number of cases of Long Covid in the UK, especially in the absence of a diagnostic test; however, the most recent national estimates suggest that around 2 million people in England and Scotland were experiencing symptoms as of March 2024 [5].

The nature of the illness, together with its prevalence, suggests that Long Covid is a significant public health problem [5]. There is a limited evidence base to inform which interventions may be effective; however, evidence on exercise-based rehabilitation has demonstrated positive effects in improving exercise tolerance, respiratory symptoms, fatigue, and cognition [6–9]. Most rehabilitation studies to date have been observational cohorts, so the effects of natural recovery versus the benefits of rehabilitation are unknown. Furthermore, previous studies have focused on hospitalised cohorts as opposed to patients who had their acute Covid managed out of hospital (‘community managed’) [10, 11].

Provision of care can vary widely between and within countries. In the UK, for example, there is guidance from NICE, the NHS Plan for Improving Long Covid services, and Long Covid-specific commissioning guidelines [12–14]. Interpretation of these guidelines varies regionally and nationally [15]. Hospitalisation status is increasingly being recognised as an inequality in itself, with access to Long Covid follow-up services being worse among patients who were never admitted to hospital [14], in comparison to hospitalised patients who have typically received more proactive follow-up [15, 16]. There is qualitative evidence to suggest that those not hospitalised may feel unsupported and disbelieved by health services [17] and some remain unsure of how and where to seek healthcare support [18].

There is ongoing research into inequalities in Long Covid care, specifically with regard to ethnicity and socioeconomic groups [19]. Early in the pandemic, it was recognised that some ethnic groups were disproportionately affected by Covid-19 [20], and, more recently, research has shown Long Covid is strongly associated with socioeconomic deprivation. This was highlighted in a recent study, which found that the odds of developing Long COVID are 46% higher on average in the most deprived areas compared to the least [21].

The proposed mixed-methods research design includes an exploratory randomised controlled trial with an embedded qualitative evaluation with framed questions to investigate the acceptability of this intervention and healthcare inequalities in access and experience. This study will provide guidance for service structure and design; building on the considerations outlined for this specific patient population [22]. It is anticipated that the findings will be transferrable and help inform the development and delivery of effective rehabilitation for other long-term health conditions.

### Objectives {7}

#### Primary objective

The primary objective of this study is to determine whether face-to-face rehabilitation increases maximal exercise capacity compared to usual care alone in nonhospitalised patients with Long Covid

#### Secondary objectives

• Determine the acceptability of the intervention based on participant’s engagement.• Seek to understand patients’ perceptions of the barriers and facilitators to face-to-face exercise-based rehabilitation in people with Long Covid.• Explore the effectiveness of a face-to-face rehabilitation programme on other symptoms commonly associated with Long Covid to include fatigue, breathlessness, reduced physical activity, health-related quality of life (HRQoL), anxiety, depression, and pain.• Use a healthcare inequalities lens to explore which demographic groups may be under-represented within Long Covid rehabilitation, with the qualitative work providing further evidence as to why this may be the case.

#### Exploratory objectives

• Optional blood tests will investigate the effect of face-to-face rehabilitation vs. usual care on systemic and cellular markers of immune ageing and immune-mediated inflammation including (but not limited to) T-cell surface and intracellular phenotype analysis (with or without stimulation) and circulating biomarkers such as antibodies, cytokines, or other circulating proteins.• Optional heart rate monitoring will investigate the effect of face-to-face rehabilitation vs. usual care on heart rate variability.

## Methods

### Trial design and setting {8 and 9}

This is a single-centre mixed-methods study comprising an exploratory randomised controlled trial (RCT) with an embedded qualitative component to explore the effectiveness and acceptability of face-to-face rehabilitation for patients with Long Covid who were not hospitalised with their acute infection. Figure 1 provides an overview of the study processes.

**Fig. 1 Fig1:**
[figure not shown]
Study flow chart {13}

This study will be conducted at the University Hospitals of Leicester (UHL) NHS Trust. Recruitment will take place at the outpatient Long Covid Clinic at UHL. Posters about this trial will be displayed within clinical waiting areas (e.g. Long Covid clinic). Recruiting directly from this medically led clinic at the point of rehabilitation referral will ensure that all participants have had a comprehensive multidisciplinary team (MDT) review, are medically optimised, and have been deemed medically appropriate to complete an exercise-based rehab programme. Ongoing medical support will be available for patients for the duration of the study.

### Participants – eligibility criteria {10}

Individuals must be willing to attend the face-to-face rehabilitation programme to participate in the RCT element of this study. Participants who are not willing or able to attend will be offered the opportunity to partake in the qualitative semi-structured interviews (phase 2) of this study.

Participants are eligible if they are over the age of 18 years old, were NOT admitted to hospital during the acute phase of their Covid infection, have a clinician diagnosis of Long Covid (from a dedicated Long Covid assessment clinic), have ongoing symptoms that may be modifiable by a rehabilitation programme (such as breathlessness, fatigue, or reduced exercise tolerance), and are willing and able to provide informed consent.

Individuals will be excluded from the study if exercise is contraindicated as outlined in the American College of Sports Medicine guidance [23], further investigation/management for an unstable comorbidity is required, exercise-based rehabilitation has been attended/completed in the preceding 6 months, hospital admission was required during their most recent acute SARS-CoV-2 infection, they have severe debilitating fatigue (home bound or bed bound) that worsens with activity — regardless of formal post-exertional malaise/myalgic encephalomyelitis (ME) diagnosis, or they are not willing or unable to provide consent.

### Who will take informed consent? {26a}

Consent will be sought and received by a member of the study team who has undergone appropriate consent training and is delegated to do this. Seeking informed consent will include explanations of the purpose of the research, the procedures of the study, any risks/benefits of participating in the research, and the participants’ right to withdraw at any point of the research. The participant will be able to ask any questions they have, and a participant information sheet written in lay language will be used to support this discussion.

### Additional consent provisions for collection and use of participant data and biological specimens {26b}

The RCT consent form will include optional tick boxes to consent for the additional exploratory outcome measures of blood inflammatory markers and heart rate variability and a ‘consent to be contacted for focus groups/interviews’ tick box. There will be a separate consent form to consent patients to the qualitative elements of the study.

Should patients choose to conduct their qualitative interview or focus group via remote means (telephone or videocall), informed consent may take place remotely, and an adapted ‘Remote Qualitative Consent form’ will be used. This will include a statement of fact (i.e. ‘I confirm that the participant has read and understood the PIS……’, ‘I confirm that the participant has had the opportunity to ask questions…’). The statements confirm that each section has been discussed, understood, and agreed with by the participant. This is then signed and dated, with a copy sent to the participant for their records by email/post.

Participants who consent to be contacted, but then decline to consent to the RCT element, will be asked whether they would be willing to participate in a semi-structured interview.

### Interventions {11d}

#### Phase 1 - The RCT

Both groups will receive the usual standard of care as defined by the National Institute for Clinical Excellence (NICE) COVID-19 guidance [24]. Implementing a twice-a-week rehabilitation programme for 6 weeks or usual care will not require alteration to usual care pathways (including the use of any medication), and these will continue for both trial arms. Participants will not be able to take part if they are currently taking part in another intervention research study.

### Face-to-face rehabilitation (intervention) {11a and 11c}

Individuals will complete an individualised symptom-titrated programme of exercise, education, and self-management for 6 weeks. The programme will comprise two supervised sessions per week delivered by healthcare professionals.

Six weeks have been purposefully selected as the intervention period to align with current clinical provision in Leicester. Aligning the intervention period with that used clinically will consolidate clinical expertise and support implementation.

The rehabilitation programme will consist of aerobic exercise (i.e. treadmill/ground walking at 80% of the incremental shuttle walk test (ISWT) speed where tolerated and lower-limb cycling on a static bike) and resistance exercise training (upper and lower limb strength exercises). The exercise intensity and duration will be tailored to the individual’s current abilities, assessed in their first visit.

In addition to the supervised sessions, patients will be asked to perform home-based exercise sessions which align with the supervised sessions to include the following: daily walking, three aerobic exercise sessions, and one resistance exercise session each week. Participants will be asked to record their progress in a self-reported diary, which will be used in conjunction with self-reported symptoms at the face-to-face sessions for the delivering clinicians to monitor symptoms and guide exercise modifications and progression.

Each rehabilitation session will include an educational discussion (approx. 30–60 min) delivered by a member of the multidisciplinary team. These discussions will be facilitated by information sheets saved from the Your COVID Recovery (YCR) website repository. Topics covered will include the following: getting moving again, managing activities of daily living, breathlessness, fatigue management, and recognising symptoms of worsening in response to exercise, fear and anxiety, mood and coping, memory and concentration, cough, eating well, sleep hygiene, goal setting, headaches, managing symptom exacerbation and fluctuations, and returning to work. At the end of each session, there will be an opportunity for discussion and question and answer.

Signs of post-exertional malaise and post-exertional symptom exacerbation will be monitored using the DePaul Symptom Questionnaire–Short Form (DSQ-SF) [25], modified Borg breathless scale [26], and Borg rate of perceived exertion (RPE) [27], and results were discussed by the healthcare professional with the participant at the start of each session. Adjustments to the exercise programme, or onward referral, will be made as necessary, and patients may be removed from the study if adverse events occur.

Clinical staff responsible for delivering the intervention have become experts in this now well-established intervention. Training will be provided to any new staff, and a competency scheme is in place to ensure there is standardisation of care.

### Usual care (control) {6b}

Participants in the control arm will receive usual care for 6 weeks. Routine clinical care will continue, such as medical follow-up, mental health service provision, and other specialist services.

#### Phase 2 – one-to-one semi-structured interviews

Interviews will be conducted by the lead researcher with those that declined (elected not to participate in the intervention at all) and those that dropped out of the programme (commenced but did not complete the intervention) to explore why people did not attend/complete in order to develop an understanding of the barriers to attendance. The data gathered from these interviews will help to identify and explore any healthcare inequalities that may be evident and whether there are any differences in the demographics of those who choose not to attend/complete. These will take place either face to face or virtually (by telephone or video conference) depending on the participants’ preference. It is expected that the interviews will take between 45 and 60 min depending on the responses.

The acceptability framework will inform the topic guide [28]; however, the nature of semi-structured interviews offers the researcher agency to adapt the interview for each participant depending on the answers provided.

#### Phase 3 - face-to-face focus groups

Focus groups will be conducted by the lead researcher ([name]) who will act as the primary moderator and a research associate who will act as an assistant moderator to take field notes. Completers of the intervention group will be invited to take part in a focus group of around 8–10 participants. The aim of the focus groups will be to explore the facilitators to attendance and any healthcare inequalities that may be apparent. The acceptability framework will inform the topic guide, which will be evaluated by the patient advisory group prior to finalising. It is expected the focus group will take between 60 and 90 min.

Community language interpreters will be provided as required in any of the study phases.

All interviews and focus groups will be audio recorded with permission and transcribed verbatim removing all identifiable information to ensure anonymity.

Reimbursement of expenses will be made to those who travel to take part in either the focus group or a semi-structured interview in line with NIHR guidance [29].

### Criteria for discontinuing/modifying interventions {11b, 18b, 21b and 22}

Due to the nature of the trial, there are no formal stopping rules as no problems detrimental to the participant are anticipated (supported by data from the hospitalised trial [30]). The intervention will be discontinued if the participant withdraws consent or if a change in circumstance results in the participant becoming unsafe to engage in the intervention. Data collected up until the date of withdrawal will remain in the analysis with participants’ consent.

As the intervention is individualised, any modifications will be determined through discussions between the patient and healthcare professional. Reasonable adaptations to exercise will be made based on clinical judgement and participant need.

Participants will be carefully monitored with particular attention to those displaying signs of post-exertional malaise (PEM) and post-exertional symptom exacerbation (PESE) via the DePaul outcome measure. Steps have been taken to ensure those with known PEM/PESE are not recruited to this trial to ensure their symptoms are not worsened by rehabilitation. If it appears that someone is experiencing PEM/PESE during the intervention phase, then they will be suspended from the trial, upon discussion with the individual, and referred to the appropriate clinic(s).

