#### Primary outcome

Maximal exercise capacity was measured by absolute change in ISWT distance (in metres) 6 weeks after baseline (±2 weeks). The ISWT will be performed in line with technical standards [32]. In brief, the test is an externally paced, incremental test that requires the patient to walk around a 10-m (m) course at a target speed dictated by audio bleeps. As a maximal, progressive test, the walking speed starts slowly but increases each minute, with the test terminated when the patient is no longer able to keep up with audio cues or by the assessor if the required speed is not attained. The test will be performed twice pre-intervention for familiarisation, with the highest distance achieved used for exercise prescription (ESWT speed). The test will be repeated once after the intervention (Table 1).

**Table 1 Tab1:** Secondary outcome measures

Acceptability	Physical Measures	Questionnaires
Quantitative measure of completion in the intervention group	Short physical performance battery (SPPB) [33]	Generic HRQoL: EQ-5D-5L [34]
Qualitative evidence via focus groups and semi-structured interviews	Physical activity monitoring: ActiGraph accelerometer device [35]	Fatigue: Functional Assessment of Chronic Illness Therapy Fatigue Scale (FACIT-Fatigue) [36]
	Maximum isometric quadriceps strength (kg) [37]	Depression: Patient Health Questionnaire (PHQ9) [38]
	Endurance Shuttle Walk Test (ESWT) (seconds) [39]	Anxiety: Generalised Anxiety Disorder 7-item scale (GAD7) [40]
		Breathlessness: MRC Dyspnoea scale [41]
		Covid-specific HRQoL: Modified C19-YRS [42]
		Cognitive Function: Montreal Cognitive Assessment (MoCA) [43]
		Post Exertional Malaise: DePaul Symptom Questionnaire Short Form (DSQ-SF) [25]

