### Recruitment {15}

Patients will be recruited at the point of referral from the Long Covid Assessment Service into the Long Covid Rehabilitation Service. This referral is only completed when the assessing clinician has deemed them ready and clinically suitable for a rehabilitation programme.

Potential participants may be directly issued a patient information sheet (PIS) by their clinical team and asked if a member of the study team can contact them to discuss the trial either over the phone or via email (as per their preference). Patients invited at the point of referral will use the reply slip on the foot of the PIS and the included prepaid envelope to indicate they wish to be contacted by the study team. Potential participants that self-identify or are referred by their GP will be investigated and, if appropriate, invited to the Long Covid clinic prior to the commencement of the trial.

Personal information will not be accessed or reviewed by the study team until consent to contact has been obtained.

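### The article says people with known PEM/PESE are kept out of the trial, but its only listed exclusion that mentions PEM is limited to the home bound or bed bound

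*Protocol article*

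**What the plan says.** Three parts of the protocol article bear on this.

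- **Safety text** (Criteria for discontinuing/modifying interventions {11b, 18b, 21b and 22}): "Steps have been taken to ensure those with known PEM/PESE are not recruited to this trial". The reason given is that rehabilitation should not make their symptoms worse. A backstop follows: "If it appears that someone is experiencing PEM/PESE during the intervention phase, then they will be suspended from the trial, upon discussion".
- **Entry rule** (Participants – eligibility criteria {10}): a person is excluded if "they have severe debilitating fatigue (home bound or bed bound) that worsens with activity", whether or not PEM or ME has been formally diagnosed. On the inclusion side, candidates must "have ongoing symptoms that may be modifiable by a rehabilitation programme (such as breathlessness, fatigue, or reduced exercise tolerance").
- **Clinical gates**: under Trial design and setting {8 and 9}, participants come through a medically led clinic with multidisciplinary review and "have been deemed medically appropriate to complete an exercise-based rehab programme". Under Recruitment {15}: "This referral is only completed when the assessing clinician has deemed them ready and clinically suitable for a rehabilitation programme".

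**The concern.** The safety text covers everyone with known PEM/PESE. The entry rule excludes on severity and confinement. These are different populations, and the difference is the ambulatory patient whose PEM/PESE is already known.

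By the article's own reasoning, exclusion is there to prevent harm from exercise. If the written criteria do not require it, whether such a patient enters depends on how an individual clinician judges general suitability. The article also states that there are no formal stopping rules and no data monitoring committee, so the entry criteria carry more of the protective load than they otherwise would.

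There is a smaller consequence for the trial itself. A patient could be eligible on paper, be randomised, and then be suspended for a condition known beforehand. That is an avoidable loss in a trial of 56 planned participants that needs 23 per group for its primary comparison.

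**Working it through.** No figure in the plan is at issue and no arithmetic applies. The check is whether the entry rule delivers what the safety text promises.

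**Step 1: scope of the two statements.**

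| | Safety text | Exclusion that mentions PEM |
|---|---|---|
| What triggers it | Known PEM/PESE | Severe debilitating fatigue that worsens with activity |
| Severity limit | None | Home bound or bed bound |
| Role of a diagnosis | Being known is enough | Neither required nor sufficient |

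**Step 2: run a test case through the criteria.** Take an adult with clinic-diagnosed Long Covid, never admitted with COVID-19, who has fatigue and reduced exercise tolerance. PEM is recorded in the notes, but the person leaves home and can attend sessions.

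- Inclusion: age, no admission, clinic diagnosis and consent are met. Fatigue and reduced exercise tolerance are among the named qualifying symptoms, provided they may respond to rehabilitation. The criterion says nothing either way about PEM.
- Exclusion 1, contraindication to exercise under cited outside guidance: PEM is not named in the article, and the guidance is not at hand.
- Exclusion 2, unstable comorbidity needing investigation or management: not triggered by the case as described.
- Exclusion 3, exercise rehabilitation in the previous 6 months: not triggered.
- Exclusion 4, admission during the most recent acute infection: not triggered.
- Exclusion 5, severe fatigue: not triggered, because the person is neither home bound nor bed bound.
- Exclusion 6, consent: not triggered.

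Unless the outside guidance in exclusion 1 lists PEM, the patient passes.

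**Step 3: the clinical gates.** Both ask for a general judgement of suitability. Neither names PEM/PESE. A clinician may refuse the referral because of PEM, but nothing written obliges that.

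**Step 4: when the other safeguards act.** The DePaul questionnaire (DSQ-SF) is listed at enrolment in Table 2, but no eligibility threshold is stated for it. Review of PEM signs takes place at the start of each rehabilitation session, and suspension is written for the intervention phase. The ISWT, which the article describes as a maximal test, comes earlier: "The test will be performed twice pre-intervention for familiarisation". It is done in both arms. At that point the patient has passed the clinic's suitability judgement and has an individualised baseline assessment that includes Long Covid history. There is still no written PEM/PESE rule.

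**Result.** The test patient can be eligible under the listed criteria, while the safety text says steps have been taken to ensure that such a patient is not recruited.

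**The case against.** The best defence is that the safety text speaks of steps, not of a listed exclusion, and that the article describes such steps. These are recruitment only through a medically led clinic, multidisciplinary review, referral only once a clinician judges the patient ready, and exclusion for exercise contraindications. A patient whose PEM makes exercise unsuitable ought to fail one of these. During the programme, exercise is titrated to symptoms and PEM signs are reviewed every session. An article also condenses its full protocol, and that protocol or the clinic's referral criteria may name PEM.

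Much of this stands. The gates may work well, and the documents do not show what staff apply in practice. But the article prints both its eligibility criteria and its assurance, and the two do not match. This is therefore more than detail left to a fuller document. The assurance claims to ensure non-recruitment, and a general judgement that does not name the condition cannot be read as ensuring that.

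A reader might infer more than the documents support, in three ways:

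- *That patients with known PEM are being enrolled, or that screening staff ignore PEM.* No screening form, referral criteria or enrolment data are shown.
- *That nothing but the entry rule protects a patient at the baseline walk tests.* The clinic gates and the individualised baseline assessment come into play too, and medical support is available throughout.
- *That the exercise schedule measures the harm.* The home programme of "daily walking, three aerobic exercise sessions, and one resistance exercise session each week" and the supervised sessions are what any rehabilitation participant is offered, before tailoring. They do not indicate how many people are affected or how badly.

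**Conclusion.** The concern holds as a conflict between a stated safety assurance and the stated entry rule. As the article is written, an ambulatory patient with known PEM/PESE can meet every listed criterion, undertake the baseline maximal tests and be randomised to exercise. Clinicians may prevent this, but no written criterion requires them to.

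The size cannot be given: the documents do not report how many clinic patients have ambulatory PEM/PESE. The conclusion rests on two readings. The first is that the assurance, which has no severity qualifier, means any severity. The second is that the cited exercise guidance does not itself list PEM as a contraindication, which cannot be checked here. The correction should be made because it concerns participant safety and is cheap. It is not evidence that harm has occurred, and it does not call the primary comparison into question.

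**What to change.** **Preferred.** Add to the exclusions: *known PEM/PESE of any severity*. Keep the home-bound/bed-bound criterion, which also catches severe activity-worsened fatigue that has no formal diagnosis.

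**Alternative.** If ambulatory PEM is meant to be eligible, narrow the safety sentence so that it matches the existing exclusion, and make sure participants are told of the risk.

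**Those already enrolled.** Recruitment began in November 2024. Alert the treating clinicians to any recorded PEM/PESE, and apply the existing suspension rule only if PEM/PESE appears during the intervention. Do not suspend on past notes alone. The rule is written for symptoms appearing in the intervention phase, and using it on history could remove people from the rehabilitation arm only, after randomisation.

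**Cost.** One amendment by the route under Oversight and monitoring, one added exclusion line for screening, and a message to treating clinicians. No new visit or instrument is needed. The recruitment pool becomes somewhat smaller, in a trial that already expects recruitment to be hard, and the results apply more narrowly; the safety sentence already implies both. A criterion based on *known* PEM/PESE still depends on what the clinic has recorded, but that is also the scope of the assurance.
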